## **6. OBJECTIVES AND OUTCOME MEASURES**

Please refer to objectives and outcomes in section 3.

## **7. STUDY DESIGN**

This is a prospective randomised controlled trial (RCT) with an embedded evaluation and optimisation of the recruitment process (QuinteT) to assess the feasibility of progression to a definitive RCT. Participants will be recruited from hospitals across England.

Participants are expected to be involved in the study for approximately 2-3 months. They will be asked to attend hospital visits for screening, pre-operatively (on the day of surgery), and 30 days post-operatively. They will also remotely complete questionnaires at 1-3 days pre-operatively and have a semi-structured qualitative interview over the phone. The intervention will be delivered over the pre-operative period. Appendix A shows the study flow-chart.

## **8. PARTICIPANT IDENTIFICATION**

### **8.1. Study Participants**

Participants with BMI  $\geq 28$  kg/m^2 listed for colorectal cancer surgery aged  $\geq 18$  years.

### **8.2. Inclusion Criteria**

- Participant is willing and able to give informed consent for participation in the study.
- Able to communicate in English or has a relative/friend/carers acting as interpreter.
- Aged 18 years or above.
- BMI  $\geq 28$  kg/m^2 (or BMI  $\geq 25$  kg/m^2 for people of Black, Asian, or minority ethnic origin).
- Listed for curative elective colorectal resection for cancer.
- If neoadjuvant treatment is indicated, it must have been completed.
- Performance status 0-2.

### **8.3. Exclusion Criteria**

The participant may not enter the study if ANY of the following apply:

- $\geq 10\%$  self-reported weight loss in the 6 months before the screening visit

- <20 days from the screening visit until surgery.
- Having allergy to soy.
- Documented stage 4-5 kidney disease.
- Documented severe heart failure (defined as New York Heart Association grade 3 or 4).
- Previous bariatric surgery.
- Type 1 diabetes.
- Currently on warfarin.
- Currently on insulin with a previous episode of diabetic ketoacidosis.
- Radiological suspicion of imminent intestinal obstruction or endoscopic evidence of an impassable tumour.
- Pregnancy, breastfeeding, or planning pregnancy during the course of the trial.
- Any other significant disease or disorder which, in the opinion of the Investigator or healthcare professional, may either put the participants at risk because of participation in the trial, or may influence the result of the trial, or the participant's ability to participate in the trial.
- Currently taking part in other interventional clinical trials unless agreed in advance by all trial teams (participation in observational studies is allowed).

A list of trials that co-enrolment has been agreed by all trial teams and a list of trials that co-enrolment has been agreed to not be allowed will be regularly updated and provided to trial sites.

## **9. PROTOCOL PROCEDURES**

A schedule of procedures is available in Appendix B.

### **9.1. Recruitment**

Participants will be recruited from NHS Trusts across England. We will aim to select sites to cover multiple geographical areas. Sites need to meet the following criteria:

- Assign a named healthcare professional (surgeon, anaesthetist, nurse, or dietitian) as local Principal Investigator
- Train staff to the trial procedures
- Have adequate staff and resources to
  - o recruit participants, conduct study assessments, and provide relevant research data (including a blinded researcher for outcome assessment)
  - o liaise regularly and as appropriate with the Surgical Intervention Trials Unit and central study team, and
  - o commit to a minimum target recruitment rate of 3 patients every 4 months (0.75 patients per month).

The recruitment pathway will be flexible within and across recruitment sites to allow for differences in cancer diagnostic and treatment pathways across patients and hospitals. In all cases, a

member of the clinical team will be the first person who will raise the option of the research study to a potentially eligible participant before that participant is formally approached by a member of the research team to discuss entering the trial.

Patients may be approached about the trial before or after the final decision to have surgery has been made to allow for as much time as possible for potential participants to consider participation. However, they will only enrol after they have been (provisionally) listed for surgery. For example, when cancer is suspected during routine checks, a member of the clinical team (e.g., the cancer nurse specialist or doctor) will inform the patient about the possibility of a cancer diagnosis and the likelihood of surgery. At this time, they will make patients aware of the trial and ask them for their verbal consent to pass their contact details to the research team. The member of the clinical or research team will provide the potential participant with a participant information sheet (PIS). A research nurse (or other member of the research team) will contact the participant to discuss the study and pre-screen potentially eligible participants with a brief phone interview to check the eligibility criteria and concomitant medication. Once the CRC diagnosis is confirmed, a research nurse (or member of the clinical or research team) will contact the potential participant for a second discussion about the trial and to book them in for a screening visit. In other cases, the first contact of a potential participant with the research nurse might be after the CRC diagnosis has been confirmed by the clinical team or after potential participants have discussed the surgical treatment options with a member of the clinical team and a decision to treat has been made.

In hospitals where participants are notified in advance that research studies are taking place and their personal information may be accessed by the research team, a research nurse (or member of the research team) may also screen relevant clinic lists and/or observe the multidisciplinary team meeting where surgical cases are discussed to flag potentially eligible participants to the clinical team.

We will create a video covering the key points of the PIS, upload it online, and direct participants to the video link to facilitate accessibility.

For colon cancers, the screening visit should be booked within the next working day (and up to 3 days) following communication to patient they have been (provisionally) listed for surgery.

For rectal cancers (<20cm from the anal verge), the decision to book the screening visit will be made following the multidisciplinary team meeting. If neoadjuvant treatment is indicated, the participant should be booked for a screening visit only following completion of neoadjuvant treatment. If neoadjuvant treatment is not indicated, the participant should be booked for a screening visit within the next working day (and up to 3 days) following communication to patient they have been (provisionally) listed for surgery.

Participants who decline to participate will be asked to provide the reasons for declining to take part by choosing all possible reasons from the following pre-defined list. This information is likely to be provided over the phone to the member of the clinical or research team and will be retained for the study without any personal identifiers (anonymously).

1. I would find it difficult to stick to the diet
2. I do not like the idea of eating shakes and soups instead of usual food
3. I am worried about potential side effects from the diet
4. Transport / distance to hospital

5. I feel unable to cope with additional requirements of me at this moment in time
6. I do not like the idea of randomisation
7. I feel uncertain that the trial will benefit me
8. I was not given adequate information
9. Other

## **9.2. Informed Consent**

The participant enrolling on the trial must personally sign and date the latest approved version of the Informed Consent form before any study specific procedures are performed.

Written and verbal versions of the participant information and informed consent will be presented to the participants detailing no less than: the exact nature of the study; what it will involve for the participant; the implications and constraints of the protocol; the known side effects and any risks involved in taking part. It will be clearly stated that the participant is free to withdraw from the study at any time for any reason without prejudice to future care, without affecting their legal rights, and with no obligation to give the reason for withdrawal.

The participant will be allowed as much time as wished to consider the information, and the opportunity to question the Investigator, their GP or other independent parties to decide whether they will participate in the study. Electronic written informed consent will then be obtained by means of electronic participant-dated signature and dated signature of the person who presented and obtained the informed consent on the eCRF. The person who obtained the consent must be suitably qualified and experienced and have been authorised to do so by the Chief/Principal Investigator. A copy of the signed informed consent will be given to the participant (via email or printed physical copy). The original signed form will be retained in the eCRF at the study site.

For consent to audio-recordings of the recruitment interactions, please refer to section 9.6.5.b and to Appendix C.

## **9.3. Screening and Eligibility Assessment**

During the screening visit, participants will provide written informed e-consent. Following informed consent, their weight and height will be measured to ensure they meet the BMI criterion. The concomitant medication will be reviewed. Each participant must satisfy all the approved inclusion and exclusion criteria of the protocol. If a participant does not meet all of the criteria, they will be recorded as a screen failure. Participants will also complete all baseline assessments.

## **9.4. Randomisation**

The randomisation software will be programmed by the clinical trials unit. There will be no paper-based back up randomisation procedure in case of emergencies.

At the end of the screening visit, participants who meet all the eligibility criteria and are keen to proceed with the study should be randomised. Queries on eligibility must be resolved before randomisation and participants who do not meet all the eligibility criteria must not be randomised. The research nurse or delegate will randomly allocate participants using a web-based central minimisation software. Eligible participants will be individually randomised with a 1:1 allocation ratio to receive either

the intervention or care as usual through minimisation with a 20% random element. The two stratified variables will be performance status (0 vs 1-2) and median age at diagnosis ( $\leq 70$  years).

The research nurse will enter the participant details to the randomisation system (initials, participant ID and research site code, confirmation of eligibility, confirmation of completion of baseline assessments, date of informed consent, and stratification factors). The system will allocate the participant and instantly inform the researcher of the allocation. The researcher will then inform the participant of their allocation.

The maximum duration between completion of the screening visit and randomisation will be 24 hours (e.g., to allow for query resolution). In such case, the local research team will contact the participants to notify them about their allocation.

If randomisation has not occurred within 24 hours but participants are still keen to continue with the study, they will have to be re-screened by checking that the time limit until surgery has not elapsed but participants will not be required to complete again the baseline assessments.

Allocation concealment is achieved as randomisation occurs after the baseline visit, the randomisation algorithm is unmodifiable and concealed from investigators and the local research teams, and the local research teams have no access to the total number of participants randomised to each group.

Following randomisation, the research team will send a letter to the participant's GP informing them about trial participation and group allocation.

### **9.5. Blinding and code-breaking**

It is impossible to blind the participants and research nurses due to the nature of the intervention. Therefore, procedures for breaking the allocation code are not applicable. However, the assessors of the future primary outcome (research nurses conducting the post-operative follow-up visit) will be blinded.

## **9.6. Description of study intervention(s), comparators and study procedures (clinical)**

### **9.6.1. Description of study intervention(s)**

The intervention is a low-energy total diet replacement programme with behavioural support.

Participants will replace all their foods with a nutritionally complete package of 4 formula products per day (such as soups and shakes (~800kcal/day)). The composition will follow regulatory guidelines.[61]

They will be advised to drink >2.5L/day of energy-free fluids (e.g., water, tea, coffee, diet soft drinks) with a provision of up to 100ml of skimmed milk for tea/coffee per day but no energy-dense drinks (e.g., alcohol).

Participants will have a 45-min introductory phone call with a dietitian to provide behavioural support and then weekly 20-minute follow-up calls. Participants will be offered the option of having the

support over video (MS Teams) if they prefer. The support aims to maintain motivation during the adjustment to formula foods and problem-solve issues that arise. This is a structured programme using weekly progress review, feedback on changes, checks on product tolerance, practical tips for mixing shakes and adding flavour, problem solving any barriers, managing social situations, coping with hunger, encouragement, action planning, avoiding and managing lapses, and behaviour change techniques to maintain motivation. In previous studies the support has been valued highly by participants.[36, 62]

The intervention will start on the day post-randomisation. Following randomisation, research nurses will provide participants a few products, so that they can start the programme the next day. The introductory phone call with the dietitian should ideally be completed on the day of or the day following randomisation. Participants will receive the rest of the products by post.

The intervention will finish approximately two days pre-surgery (depending on local guidance for standard pre-operative preparation) or when 15% weight loss has been achieved (if unexpected lengthy delays to schedule the surgery occur), whichever is earlier.

One in 5 people experience an adverse, mostly mild, event due to the intervention.[21] Constipation (1 in 7), fatigue (1 in 12), headache (1 in 17), and dizziness (1 in 22) are the most common Adverse events (AEs) albeit mild (only 11% were moderate or severe), reduce in intensity over time and disappear as soon as the intervention is discontinued.[21, 22] Here, the risk of constipation will be proactively managed with advice for high energy-free fluid intake (>2.5 litres/day) and a fibre supplement.

Participants will receive the intervention on top of the local standard care pathway that may include advice and support on pre-habilitation.

#### Medication adjustment

**Type 2 diabetes:** As per the NHS England and NHS Improvement guidance for this intervention, participants who are managing their diabetes with sulfonylureas (gliclazide, glibenclamide, glimepiride), meglitinides (Repaglinide, Nateglinide), or SGLT2 inhibitors (dapagliflozin, canagliflozin, empagliflozin, ertugliflozin) will be instructed to stop them on the first day of the intervention due to safety risks, including the risk of hypoglycaemia (sulfonylureas, meglitinides) or risk of ketoacidosis (SGLT2 inhibitors). If participants do not stop these medications, they must not start the intervention. Participants will be required to continue attending their diabetes review appointments /monitoring at their GP as usual and to notify their GP if they disengage from the intervention (as medication may need to be restarted).

**Hypertension:** If the blood pressure at the screening visit is uncontrolled (If blood pressure is considered uncontrolled at time of referral (systolic  $\geq 140$ mmHg OR diastolic  $\geq 90$ mmHg), no changes to blood pressure lowering medications will be made.

If the blood pressure at the screening visit is controlled (both systolic <140mmHg AND diastolic <90mmHg), one blood pressure medication should be adjusted on the first day of the intervention. Medication being used specifically and solely for managing blood pressure, in a particular participant, are the priority for adjustment. The agent that has been added last according to current NICE (National Institute for Health and Care Excellence) guidance should be stopped. If not being used for other indications, this would be (in order of stopping first):

- a. Spironolactone or alpha blocker or beta blocker
- b. Thiazide diuretic (or calcium channel blocker)
- c. Calcium channel blocker (or thiazide diuretic)
- d. Angiotensin-converting enzyme inhibitor or Angiotensin receptor blocker

If the patient is taking medications which affect blood pressure but ALL are being used for other indications (i.e., none are being used solely to manage blood pressure), clinical judgement and shared decision making should be used taking into account the blood pressure reading. In this case, the dose should be cautiously reduced (e.g., to the next lower dose) instead of stopped.

#### Self-monitoring of blood pressure and blood glucose

Intervention participants taking insulin or medication for hypertension will be asked to self-monitor their blood glucose or blood pressure, respectively, and report out of range values to the dietitian who will communicate this to the participant's GP within 3 working days (or earlier if deemed necessary). Participants will be counselled about symptoms of hypoglycaemia and postural hypotension and advised of when and how to seek appropriate support. They will receive blood pressure/glucose monitors if they do not own one.

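### Protocol 9.6.1 sets day-1 rules for three oral diabetes drug classes and for blood pressure drugs, but requires no insulin decision before the ~800 kcal/day diet starts

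*Combined protocol and SAP*

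**What the plan says.** Protocol 8.3 excludes type 1 diabetes. Among other insulin users it excludes only those described as "Currently on insulin with a previous episode of diabetic ketoacidosis", so the rest can enter. On timing, 9.6.1 states: "The intervention will start on the day post-randomisation". The diet replaces all food with formula products at about 800 kcal/day.

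The medication adjustment text in 9.6.1 tells participants with type 2 diabetes to stop sulfonylureas, meglitinides and SGLT2 inhibitors on the first day. The reason given is safety, "including the risk of hypoglycaemia (sulfonylureas, meglitinides"), with ketoacidosis named for SGLT2 inhibitors. The rule is firm: "If participants do not stop these medications, they must not start the intervention". The text attributes this to NHS England and NHS Improvement guidance. Blood pressure drugs also have a day-1 rule, which depends on the reading at screening.

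Insulin appears only in the self-monitoring text that follows: "Intervention participants taking insulin or medication for hypertension will be asked to self-monitor their blood glucose or blood pressure, respectively". These participants are to "report out of range values to the dietitian who will communicate this" to the GP within 3 working days, or sooner where thought necessary. They are counselled on hypoglycaemia symptoms and on when and how to seek help, and are given a monitor if they have none.

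**The concern.** For blood pressure, self-monitoring is added to a rule about the drugs themselves. For insulin, self-monitoring stands alone. A participant taking both a sulfonylurea and insulin is told what to do with the first and nothing about the second, although 9.6.1 already recognises drug-induced hypoglycaemia on this diet as a reason to act on day 1.

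The stake is patient safety. A site can follow the written protocol exactly, start an insulin user on the diet with insulin unchanged, and pass a low glucose value to the GP up to 3 working days later. Safety is also progression criterion 5, so a preventable event would bear on that judgement.

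**Working it through.** The plan gives no figure to reproduce here, so the main check sets the rules in 9.6.1 side by side.

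| Treatment | Rule on day 1 | During the diet |
|---|---|---|
| Sulfonylureas, meglitinides | Stop, or do not start the diet | Usual GP diabetes review |
| SGLT2 inhibitors | Stop, or do not start the diet | Usual GP diabetes review |
| Blood pressure drugs | Uncontrolled: no change. Controlled: stop one agent in a stated order, or cautiously lower a dose by clinical judgement if all agents serve other indications | Self-monitoring, counselling, relay to GP |
| Insulin | None stated | Self-monitoring, counselling, relay to GP, usual GP diabetes review |

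Next, could another step supply the missing decision before day 1?

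- **Pre-screening call (9.1).** On one recruitment route the research team will "pre-screen potentially eligible participants with a brief phone interview to check the eligibility criteria and concomitant medication". No action on insulin follows.
- **Screening visit (9.3, 9.6.4).** Medication is recorded and reviewed. Insulin use will therefore normally be known, but no action is specified.
- **GP letter (9.4).** It is sent after randomisation, "informing them about trial participation and group allocation". It need not arrive before the diet starts the next day, and no reply is awaited.
- **Dietitian's first call (9.6.1).** This is ideally on the day of randomisation or the day after. It is not a prescribing decision.
- **Investigator discretion (8.3, 9.10).** It allows exclusion or discontinuation, but it is general.

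None of these requires anyone to decide what happens to insulin before the diet starts.

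**Length of diet.** Screening and randomisation are on day 0, the diet runs from day 1, and it ends about 2 days before surgery.
- Shortest window allowed by 8.3: 20 − 2 = about 18 days.
- Typical 4-week window (section 5): 28 − 2 = about 26 days.

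**Relay limit.** Three working days from a Monday or Tuesday is 3 calendar days. From a Wednesday, Thursday or Friday it is 5.
- Share of an 18-day diet: 3/18 = 17% to 5/18 = 28%.
- Share of a 26-day diet: 3/26 = 12% to 5/26 = 19%.

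This limits notification of the GP. It does not measure risk, because participants are told separately how to seek help.

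**Price of a delayed start.** Section 2 gives 5% weight loss in 20 days and section 5 gives 7% in 4 weeks.
- Rate: 5/20 = 7/28 = 0.25 percentage points per day.
- Average loss over 18 days: 18 × 0.25 = 4.5%, already under the 5% adherence cut-off.
- Average loss over 26 days: 26 × 0.25 = 6.5%, a margin of (6.5 − 5)/0.25 = 6 days.
- Loss per delay: 1 to 2 days cost 0.25 to 0.5 points. A delay of 3 to 7 days (assumed) would cost 0.75 to 1.75 points.
- One participant of 36 falling below 5% moves the adherence proportion by 1/36 = 2.8 points.

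**Number affected.** The documents give no diabetes or insulin prevalence. Purely as an assumption, take 15% to 25% with type 2 diabetes and 10% to 25% of those on insulin.
- Low end: 0.15 × 0.10 × 36 = 0.5 participants.
- High end: 0.25 × 0.25 × 36 = 2.3 participants.

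These counts restate the assumed inputs, and the conclusion does not rest on them.

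**The case against.** The best reply is that monitoring was a deliberate choice. Amendment 3.0 lists revised exclusion criteria on insulin use, so insulin eligibility was considered. Insulin users who remain eligible have their own pathway, and the relay can already be faster than 3 working days. That stands against any suggestion that insulin was forgotten. It does not supply a decision before the start, because every element of the pathway either informs the participant or acts after a value has been seen.

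A second reply is that the comparison is uneven. A reader might infer that 9.6.1 asks for a prescriber's decision on the oral drugs and omits it for insulin. It does not: participants are simply instructed to stop those drugs. A uniform stop instruction can suit drugs that everyone can be told to stop, and none is proposed here for insulin. What remains of the comparison is that the other treatments have a day-1 rule and insulin has none.

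A third reply is that the cited NHS guidance, the site training and the GP letter are not in the documents, and any of them may already require an insulin decision. This stands. It limits the finding to what the protocol states.

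Finally, a check placed after randomisation could delay the diet while a reply is awaited, and the participant would still count in the main analysis after surgery. No document gives a prescriber's response time. This also stands, and it is why the check belongs at screening where possible.

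**Conclusion.** The point holds as a gap in the written safety procedure. The protocol does not require an insulin decision before an eligible insulin user starts the diet, and its response to abnormal glucose has an undefined trigger and a limit of 3 working days.

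A reader might go further and infer that hypoglycaemia risk is unmanaged, or that sites will leave insulin unchanged. The documents do not support that. They show safeguards during the diet, and they do not show what the NHS guidance says or how sites act. Whether the existing pathway is clinically sufficient is a matter for the trial's clinical advisers.

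The number affected is probably small but cannot be derived. No estimate, sample size or progression threshold is wrong. The change is worth making because it is specific, cheap and concerns a foreseeable harm.

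**What to change.** Amend 9.6.1 in two respects.

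1. Flag insulin use at pre-screening or screening. Where possible before randomisation, obtain and record an insulin plan from the responsible prescriber or a suitably qualified site clinician, to apply if the patient is allocated to the diet. An intervention participant on insulin does not start the diet until that plan is recorded. Clinical advisers set the content; no dose is proposed here.
2. Define out-of-range glucose values. For insulin users, have the dietitian escalate them the same day.

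If the NHS guidance or site material already requires the plan, a sentence in 9.6.1 saying so would cover the first item. If recruitment has closed (planned to November 2024), the change belongs in the definitive trial's protocol.

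The cost is one paragraph, one eCRF check, and some plans obtained for insulin users later allocated to usual care. The main downside is a late start of unknown length for a few intervention participants. It matters most in the shortest window, where the average loss is already near the 5% cut-off. Checking at screening limits the delay but cannot always prevent it: for patients not awaiting neoadjuvant treatment, screening is booked within about 1 to 3 days of the patient hearing of the listing, and randomisation follows within 24 hours. QuinteT Step 4 already inspects logs of the time from randomisation to diet start, so any delay would be visible.
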